**5.0 DATA ANALYSIS PLAN AND POWER ANALYSIS**

Descriptive statistics will be used to summarize the data on all participants to understand the uni- and multi-dimensional characteristics of their distribution. Clustering of observations at multiple levels will be evaluated to provide guidance for selecting bias correction method and multilevel modeling approaches. We will further evaluate missing data patterns and potential bias that could be incurred by participants’ dropout.

For Objective 1, latent growth mixture modeling [(Ram & Grimm, 2009)](https://www.zotero.org/google-docs/?broken=pb8heR) will be primarily applied to permit a person-centered approach for identification of homogeneous subgroups of individuals with distinct longitudinal outcome trajectories across our three co-primary outcome measures respectively. Fit indices (e.g. AIC and BIC), Lo-Mendell-Rubin likelihood ratio test, theoretical considerations, and clinical relevance will guide the decision of the optimum number of classes to represent the growth trajectories of personal recovery, disability, and community functioning. Given the heterogeneity of our sample particularly on age range and illness stages, it is important to assess measurement invariance and utilize methods (e.g., moderated nonlinear factor model [(Curran et al., 2014)](https://www.zotero.org/google-docs/?broken=wDzov8) that accommodate time-varying constructs over subsamples.

Further, we will adopt two multivariate longitudinal approaches, cross-lagged panel [(Hays et al., 1994)](https://www.zotero.org/google-docs/?broken=Ndb4YR) and parallel processes [(Wright et al., 2013)](https://www.zotero.org/google-docs/?broken=LLqNhv) models, to model the longitudinal outcome measures simultaneously. The former is a more theory based approach that can test directional effects that one variable has on another at different points in time, for example, earlier measures of functioning may predict later measures of disability. The latter could be used to associate multiple longitudinal trajectories with respect to their growth characteristics, for example, the slopes of growth trajectories of different outcomes may be associated with each other. In conjunction with growth mixture modeling under the accelerated longitudinal design, these methods could provide a more comprehensive view of the outcome measures of interest.

For Objective 2, we will associate the membership of the subgroups and thus the characteristics of these trajectories with sociodemographic and treatment factors, psychopathology, physical health, and biological measures at baseline by treating probabilistic membership as the dependent variable in the predictive models. We will apply structural equation modeling that combines the latent growth mixture model that determines the membership of the subgroups, measurement model that reduces the dimension of the predictors, and predictive model that links them into one step using simultaneous equations.

For objective 3, data analysis and outcomes are articulated in section 3.11, with further delineation taking place as part of the co-design process and pilot intervention designs.

For our exploratory objective, we will utilize correlational analyses to investigate relationships between temporal patterns emerging from topic modeling with study variables collected prospectively from study participants. We will also use general linear model analyses as appropriate to investigate differential characteristics between longitudinal outcome trajectory subtypes. These temporal patterns will also be examined as potential predictors for trajectory subtype membership in line with the methods employed for objective 2.

Overall retention rate is expected to fall within the acceptable range for statistical correction. Every effort will be made to prevent dropouts/missing data, and to complete relevant assessments for participants who drop out. Two statistical approaches, full information maximum likelihood estimation [(Arbuckle, 1996)](https://www.zotero.org/google-docs/?gONPAh) and multiple imputation methods [(Schafer, 1997)](https://www.zotero.org/google-docs/?Uh3flg) will be utilized when appropriate. As is typical in longitudinal research, we anticipate non-random missing data. Sensitivity analysis will be conducted to evaluate the impact of non-random missing data.

Sex and Gender Based Analysis

For the first two primary objectives, we will conduct additional analyses based on biological sex and gender respectively, based on data captured through the PhenX toolkit demographics measure. For Objective 1, we will determine the longitudinal functional trajectories within sex/gender groups across three domains and examine if there are substantial differences between sex/gender groups and if necessary, test Hypotheses 1a and 1b within sex/gender groups as a supplement analysis. For Objective 2, in addition to examining sex/gender as a main effect in predicting functional trajectories at the person level, we will further assess if it interacts with other sociodemographic, treatment factors, psychopathology, physical health, and biological measures in the predictive models.

Statistical Power and Sample Size

We have assessed statistical power for the following targeted analyses aimed to, a) identify distinct longitudinal functional trajectories of individuals with SSDs; b) establish predictive models to associate personal factors with growth trajectories; and c) provide feasibility indices for future interventions. Assuming that we will have approximately four distinct longitudinal trajectories, through a Monte-Carlo study we concluded that with a sample of n=1000 we have sufficient power (0.80) to correctly enumerate the classes when they are evenly distributed and reasonable power (0.68) when they are not. In the latter, we assumed that the smallest class only takes up 15% of the total sample. Further, we concluded that we have abundant power (0.91) to detect linear trend of small change over time (effect size of 0.20 between two consecutive waves) even for the smallest class (n=112). To identify associations between predictors (e.g., social determinants) and group membership of the different trajectories, we also anticipate to have sufficient power (0.82 to 0.85) for detecting a small odds ratio (OR = 1.68) depending on the distribution of the predictors. In addition, this study will provide reliable estimates for feasibility indices for future interventions. Assuming that only one fifth of the sample participate in a planned co-designed intervention, we will be able to attain a small margin of error of 6.9% for the recruitment rate, 6.0% for attrition and 6.4% for response rate. It also yields a power of 0.86 to detect a moderate effect size on a 1:1 design. For all aforementioned power estimation, we assumed 25% overall attrition and used .05 as the significance level.

Recruitment and Sampling

Recruitment of participants for this study will take place across all outpatient and inpatient clinical services at CAMH where individuals with SSDs may be receiving care, and include both new and existing patients receiving clinical services. Sequential cohorts of participants will be recruited based on duration of illness, enabling an accelerated longitudinal design for this study that will serve to maximize coverage of longitudinal functional trajectories across illness stages. Through regular monitoring of participant recruitment, we will balance recruitment across these multiple cohorts. Core research assessments will mirror measurement-based care assessments and metabolic monitoring being implemented across these clinical services, with sharing of assessment results with the patient’s clinical team. All participants will be offered the opportunity to participate in the neuroimaging and additional laboratory/biological components of this study either as part of this study, or ideally through shared participation in existing complementary studies already taking place in the Division. Harmonization of study assessments and data sharing with existing clinical research studies will enable integration and collaboration across clinical research studies in the Division, maximize recruitment efforts, and leverage existing funded research studies for data collection. With regards to the potential participant pool from which individuals could be recruited, current patient volumes across Schizophrenia Division outpatient clinical services at CAMH, for example, indicate that over 4000 unique patients were seen over the past year, with an average of over 1900 patients seen per month. Based on these volumes, and the integration of study assessments for this proposed work within the context of routine clinical care for such patients within existing clinical services at CAMH, this study will aim to recruit 500 participants per year for 2 years, yielding a total sample of 1000 participants enrolled in this study (i.e., approximately 10 participants per week from over 15 outpatient and inpatient clinical services).

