**1.1 Objectives and Hypotheses**

**Objective 1:** Determine the longitudinal functional trajectories of individuals with SSDs across three co-primary domains consisting of personal recovery, disability, and community functioning.

**Hypothesis 1a:** Within each outcome domain, we anticipate approximately 4-5 longitudinal trajectories, consisting of early-sustained improvement, delayed gradual improvement, early improvement / delayed mild-moderate deterioration, early improvement / delayed moderate-severe deterioration, and persistent disability.

**Hypothesis 1b:** We hypothesize that early improvement in personal recovery trajectories will be antecedents of subsequent improvement in disability and community functioning trajectories, while deteriorating or persistent disability, particularly with regards to physical disability, will be early antecedents of worse community functioning.

**Objective 2:** Develop and test predictive models to accurately determine functional trajectories at the person level.

**Hypothesis 2a:** Trajectories of functioning will be differentiable based on sociodemographic and treatment factors, psychopathology, physical health, and biological measures.

**Hypothesis 2b:** A subset of these differential baseline sociodemographic, symptoms, and biological measures will enable the prediction of individual functional trajectories with high positive predictive power.

**Objective 3:** Based on the predictors of longitudinal outcome trajectory subtypes, co-design and pilot targeted real-world interventions developed with patients, family members, and service providers.

**Hypothesis 3:** The co-designed interventions targeting the individual’s longitudinal outcome trajectory will be feasible to implement, satisfactory to participants, and offer preliminary evidence of efficacy for improving longitudinal outcomes compared to treatment as usual.

**Exploratory Objective:** Develop and validate a novel automated method using natural language processing (NLP) and machine learning (ML) to interrogate electronic medical records for the ascertainment of retrospective temporal trajectories in symptom, physical health, treatment, and functional outcomes.

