Disability will be evaluated using the World Health Organization (WHO) Disability Assessment Schedule 2.0 (WHO-DAS), a 36-item measure of disability and health that is grounded in the framework of the WHO’s International Classification of Functioning, Disability and Health [(Ustun et al., 2010)](https://www.zotero.org/google-docs/?WNIYP9). The WHO-DAS enables comprehensive evaluation of individuals’ functioning across six major life domains (cognition, mobility, self-care, getting along, life activities, and participation in society) across different populations. The WHO-DAS has been shown to have good psychometric qualities including good reliability, a stable factor structure across populations, concurrent validity, and is sensitive to change over time [(Ustun et al., 2010)](https://www.zotero.org/google-docs/?4aq4iq). In order to capture diverse perspectives on participants’ trajectories over time, we will employ both the participant self-report version as a primary outcome measure, and where available will also seek input from the informant-version of the WHODAS.

*Personal and Social Performance scale (PSP)*

The PSP will be utilized to capture the trajectory of clinician/rater-measured community functioning. The PSP is an anchored version of the Social and Occupational Functioning Assessment Scale (SOFAS) from the DSM-IV that enables separate evaluations across community functioning domains for individuals with SSDs including role functioning, social functioning, self-care, and disturbing and aggressive behaviours [(Morosini et al., 2000)](https://www.zotero.org/google-docs/?DtRe8w). Ratings across these separate subscales serve to anchor global ratings of community functioning on a scale from 1 to 100. The PSP has been shown to demonstrate good test-retest and inter-rater reliability, validity, and sensitivity to change over time [(Morosini et al., 2000; Nasrallah et al., 2008)](https://www.zotero.org/google-docs/?ZtYw8F).

Secondary measures:

*Canadian Personal Recovery Outcome Measure (C-PROM)*

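### The class-number criteria for Objective 1 include no one-population comparator for skewed or bounded scores, so score shape alone can meet the class count in Hypothesis 1a

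*Protocol*

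**What the plan says.** Protocol section 5.0 makes latent growth mixture modelling the lead analysis for Objective 1, fitted to each of the three co-primary scores. It "will be primarily applied to permit a person-centered approach for identification of homogeneous subgroups of individuals with distinct longitudinal outcome trajectories". On how many classes to keep, "Fit indices (e.g. AIC and BIC), Lo-Mendell-Rubin likelihood ratio test, theoretical considerations, and clinical relevance will guide the decision". No distribution is stated for the growth factors or residuals within a class.

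The distribution of the data is mentioned only for the descriptive summaries, which are meant "to understand the uni- and multi-dimensional characteristics of their distribution". Nothing links that step to the number of classes. The moderated nonlinear factor model in the same section is there for measurement invariance across age and illness stage.

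Hypothesis 1a in section 1.1 reads "Within each outcome domain, we anticipate approximately 4-5 longitudinal trajectories" and then names the course of each. In section 3.3 the RAS has 22 items scored 0 to 4, and the PSP gives "global ratings of community functioning on a scale from 1 to 100". The section states no range for the WHO-DAS total.

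The power statement begins "Assuming that we will have approximately four distinct longitudinal trajectories". It reports "sufficient power (0.80) to correctly enumerate the classes when they are evenly distributed", and 0.68 when they are not.

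**The concern.** A mixture of normal components can fit better than one normal component for two reasons: there are subgroups, or there is one population whose scores are not normal. AIC, BIC and the Lo-Mendell-Rubin test all work within whichever component distribution is fitted. If that is the usual normal one, none of them can tell the two reasons apart. Theory and clinical relevance could help, but they are judgement terms without a rule, and the stated theory already expects 4-5 classes.

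The classes are used later. In section 5.0, class membership is the dependent variable for Objective 2. In section 1.1, the Objective 3 interventions rest on predictors of the trajectory subtypes. In section 3.11, preliminary trajectories feed the needs assessment, although other information enters there too.

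**Working it through.** **Inputs from the protocol.** N = 1000, 25% attrition, smallest class 15%, 7 waves (months 0 to 36), PSP 1-100, RAS 22 × 4 = 88 at most if items are summed.

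**The plan's own figures.** The enumeration powers 0.80 and 0.68 cannot be rebuilt, because class separation, variances and decision rule are not given. The smallest-class size can: 1000 × 0.75 × 0.15 = 112.5 (stated as 112). So n = 750 is the right basis for a check.

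**Thresholds.** With linear growth and a covariance common to all classes, each extra class adds one proportion and two means, so 3 parameters. An extra class is accepted when twice the gain in log-likelihood exceeds
- AIC: 2 × 3 = 6
- BIC: 3 × ln 750 = 3 × 6.62 = 19.9

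The simulated 5% point of the one-versus-two-class likelihood ratio for normal data was 9.9. AIC's threshold lies below it, so AIC adds classes too easily even with normal data. BIC's lies above it.

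**Simulations.** Three sets (A, B, C) generated ONE population with n = 750 and 7 waves, and fitted normal-component growth mixtures. All score shapes are assumptions. Share of datasets in which BIC chose more than one class:

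| Assumed shape | A (60 datasets) | B (12 to 40) | C (12) |
|---|---|---|---|
| Normal | – | 0% | – |
| Skewness 0.5 | 48% | 62% | 9/12 = 75% |
| Skewness 0.75 | 95% | – | – |
| Skewness 1.0 | 100% | 100% | 12/12 |
| Bounded, about 4% at floor | – | 100% | 3/12 = 25% |
| Bounded, 12% (B) or about 16% (C) at floor | – | 100% | 12/12 |
| Bounded 0-100, score skewness 0.46, 0.70 or -0.30 | 100% | – | – |
| Bounded 0-88, baseline skewness about -0.9 | – | 100% | – |

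The skewness rows refer to the growth factors (in A, the random intercept). Skewness of 0.5 there gave an observed month-0 skewness of only 0.22 in A, which a descriptive summary could easily pass over.

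**Landing on 4-5 classes by BIC.** A: 54/60 = 90% (bounded, skewness 0.70). B: about 27%, 80% and 100% for the 4% floor, 12% floor and 0-88 scores, with K capped at 5. C: 7/12 = 58% (about 16% at floor).

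**Other criteria.** In B, Lo-Mendell-Rubin rejected one class in every dataset with skewness 1.0 or a bounded score. With normal data it rejected in 3 of 15, too few to estimate its size. AIC took more than one class in 40% of normal datasets.

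**Named courses.** A linear model cannot show a rise followed by a fall. Quadratic fits in B (12 datasets per shape) gave a class rising and then falling by more than 0.2 SD in 0% (skewed), 17% (floor) and 25% (0-88 score).

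**Does a comparator help?** In C, a one-class skew-normal growth model beat every normal mixture with two or more classes on BIC in 12/12 skewed, 12/12 strongly floored and 8/12 mildly floored datasets. When four real classes were simulated, it displaced the mixture in 0/24.

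**The case against.** The best defence is that the protocol never states normal components. Component distribution, link and reference distribution are commonly left to an analysis plan, which is not at hand. The criteria only guide the choice, the fit indices are given as examples, and the data's distribution is to be examined first. All of that stands, and it limits the point. What section 5.0 does fix is the list of criteria for class number, and no item on it compares the mixture with one non-normal population.

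A reader might infer several stronger things that the documents do not support:
- That all the criteria test K against K-1 classes. Only Lo-Mendell-Rubin does; AIC and BIC rank every K, including one.
- That a stated null of one population is being tested wrongly. Objective 1 is to determine trajectories, and no null is stated.
- That the hypothesised 4-5 is a formal selection input. It is not named as one, though nothing keeps it out of the theoretical considerations.
- That score shape alone can confirm Hypothesis 1a. The hypothesis also names courses, and the rise-then-fall pattern seldom appeared.
- That one skewed population will always be split. At skewness 0.5, BIC kept one class in 25% to 52% of datasets.
- That the power statement is wrong. Power is properly calculated under an assumed alternative; it simply does not cover the one-class case.

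**Conclusion.** The point holds in a limited form. Under the usual normal-component specification, the listed statistical criteria cannot separate distinct subgroups from one population with skewed or bounded scores, and the class count in Hypothesis 1a can be met by score shape alone. The reported Monte Carlo study does not address this.

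The size is uncertain. BIC chose more than one class in about 25% to 100% of the skewed or bounded one-population datasets and kept one class with normal data. The range rests on assumed skewness, floor rates and variances, because the protocol gives none, and many cells have only 12 or 15 datasets. At about 4% on the floor, two sets gave 100% and 25%, so the floor rate alone does not settle the size. The mechanism appeared in all three sets. The comparator removes most of the problem at little cost, which makes the change worthwhile even if the real scores prove close to normal.

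**What to change.** In section 5.0, or in the analysis plan with a reference from it:

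1. For each co-primary score, fit a one-class growth model with a skewed or bounded-response distribution beside the ordinary one-class model. Claim distinct subgroups only if the mixture beats it on BIC; otherwise report a continuum of course. Where floor or ceiling effects are visible, the bounded-response form is the natural choice, since the skew-normal comparator prevailed in only 8/12 mildly floored datasets.
2. As a sensitivity analysis, refit the chosen number of classes with the same non-normal distribution within classes.
3. State that neither AIC nor the hypothesised count of 4-5 decides the number of classes.
4. Add a one-class scenario with skewed and bounded scores to the Monte Carlo study, and report the false-class rate beside the powers of 0.80 and 0.68.

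Skew-t mixtures throughout, or a parametric bootstrap in place of Lo-Mendell-Rubin, are options and not requirements. The cost is wording, more model fitting on data already planned, and possibly fewer classes than hypothesised. No extra participants or visits are needed.

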**7.0 Risks and Benefits**

**7.1 Potential Risks and Benefits to the Participants**

The clinical assessments utilized in this study are physically non-invasive assessments associated with minimal risk. All measures have been used in prior studies with participants with mental illness and have been found to elicit minimal distress or discomfort. That said, given that some of the assessment questions are of personal nature, some individuals may be uncomfortable answering them. Patients are informed that they may refuse to answer any questions and may ask to stop at any time. Further, some participants may find the cognitive measures to be long, tiresome and frustrating at times. Measures, such as scheduled breaks, are taken to encourage participants to remain engaged. Participants are also made aware that they are free to withdraw from the study at any time, with no consequences. Lastly, the utilization of data gathered in the context of routine clinical care is intended to reduce the repetition of assessments for participants, decrease study visit duration, and minimize participant burden.

There will be minimal direct benefits to participants enrolling in this study.

With participant consent/assent, a summary of study results can be shared with the participant’s clinicians, providing additional information which may be of value to future clinical encounters and which will be available in the CAMH medical record.

**7.2 Risks Associated with the MRI examination**

There are four categories of risks to human subjects directly associated with MRI examination, including:

1. Acoustic Noise Levels: The risk associated with acoustic noise levels are related to the noise generated by the pulsing of the gradients. The risk to the participant may be temporary loss of hearing. The easiest and most reliable means of preventing hearing loss is to use disposable earplugs. Disposable earplugs or non-magnetic headphone sets will be used for all participants in this study.

1. Static Magnetic Fields: There are no established risks of exposure to magnetic fields of 3T, other than the incidental risks (listed below). Like other clinical MRI centers, our facilities incorporate a complete range of procedures to assure security of the restricted access area, and careful screening of potential participants, before they enter the restricted access area.

1. Gradient or Time-Varying Magnetic Fields: Risks associated with gradient magnetic fields are related to dB/dt (change in magnetic field over time), which can induce electric fields and currents in conductive media, including biological tissue. The MRI systems will be operated within limits already determined not to pose significant risk to humans.

1. Specific Absorption Rate (SAR): The risks associated with Specific Absorption Rate (SAR) are related to the fact that given a large enough SAR, heating of tissue may occur. Proper and routine monitoring of all RF electronics (e.g. coils, transmitters, system security, etc.) will be performed on a regular basis. There are three categories of incidental risks to all human subjects in a restricted access area. The three categories of concern are related to: (1) malfunctioning or movement of implanted metal objects (i.e., aneurysm clips, pacemakers, etc.); (2) injury from a projectile (i.e., ferromagnetic objects being attracted into the magnet); and (3) asphyxiation due to large amounts of cryogenic gasses generated during a quench (i.e., the event that occurs when a magnet makes the sudden transition from superconducting to resistively conducting). These categories of incidental risk are unlikely given the extensive set of safety checks employed by our facilities prior to scanning

Risks During Pregnancy: The risks during pregnancy are unknown. Several studies of prenatal MRI have now been published and the MRI techniques have not been demonstrated thus far to have risks. There have been no reports of adverse effects to the developing human fetus. However, because the risks have not been adequately assessed over a long period of time, women who have a confirmed pregnancy or a reason to believe they may be pregnant, as documented on the MRI Safety Screening Form, will be excluded from the MRI scan.

Risks of Psychological Distress: Some participants can experience claustrophobia while in the scanner. Participants will have the opportunity to examine this space before the scanning starts and participate in a session with a mock scanner. This study will not offer alternative procedures for participants who choose not to participate in the MRI scan or who are excluded. In our experience of scanning a large number of participants with severe mental disorders across the lifespan (e.g. autism, schizophrenia, bipolar disorder, major depressive disorder), less than 2% of these participants have been unable to complete the scanning session. However, mild psychological distress is likely to occur during the course of the conduct of the neuroimaging studies.

Risk of Incidental Findings: The possibility of unexpected or incidental findings carries with it some risks. Research scans are not designed to be used for diagnosis. In the unlikely event an atypical finding is seen on a participant’s MRI scan, a study investigator may ask a radiologist or other qualified health professional to look at the participant’s scan.

